## Abstract

**Background:**

Fungal-bacterial cocolonization and coinfections pose an emerging challenge among patients suspected of having pulmonary tuberculosis (PTB); however, the underlying pathogenic mechanisms and microbiome interactions are poorly understood. Understanding how environmental microbes, such as fungi and bacteria, coevolve and develop traits to evade host immune responses and resist treatment is critical to controlling opportunistic pulmonary fungal coinfections. In this project, we propose to study the coexistence of fungal and bacterial microbial communities during chronic pulmonary diseases, with a keen interest in underpinning fungal etiological evolution and the predominating interactions that may exist between fungi and bacteria.

**Objective:**

This is a protocol for a study aimed at investigating the metabolic and molecular ecological evolution of opportunistic pulmonary fungal coinfections through determining and characterizing the burden, etiological profiles, microbial communities, and interactions established between fungi and bacteria as implicated among patients with presumptive PTB.

**Methods:**

This will be a laboratory-based cross-sectional study, with a sample size of 406 participants. From each participant, 2 sputa samples (one on-spot and one early morning) will be collected. These samples will then be analyzed for both fungal and bacterial etiology using conventional metabolic and molecular (intergenic transcribed spacer and 16S ribosomal DNA–based polymerase chain reaction) approaches. We will also attempt to design a genome-scale metabolic model for pulmonary microbial communities to analyze the composition of the entire microbiome (ie, fungi and bacteria) and investigate host-microbial interactions under different patient conditions. This analysis will be based on the interplays of genes (identified by metagenomics) and inferred from amplicon data and metabolites (identified by metabolomics) by analyzing the full data set and using specific computational tools. We will also collect baseline data, including demographic and clinical history, using a patient-reported questionnaire. Altogether, this approach will contribute to a diagnostic-based observational study. The primary outcome will be the overall fungal and bacterial diagnostic profile of the study participants. Other diagnostic factors associated with the etiological profile, such as incidence and prevalence, will also be analyzed using univariate and multivariate schemes. Odds ratios with 95% CIs will be presented with a statistical significance set at *P*<.05.

**Results:**

The study has been approved by the Mbarara University Research Ethic Committee (MUREC1/7-07/09/20) and the Uganda National Council of Science and Technology (HS1233ES). Following careful scrutiny, the protocol was designed to enable patient enrollment, which began in March 2022 at Mbarara University Teaching Hospital. Data collection is ongoing and is expected to be completed by August 2023, and manuscripts will be submitted for publication thereafter.

**Conclusions:**

Through this protocol, we will explore the metabolic and molecular ecological evolution of opportunistic pulmonary fungal coinfections among patients with presumptive PTB. Establishing key fungal-bacterial cross-kingdom synergistic relationships is crucial for instituting fungal bacterial coinfecting etiology.

**Trial Registration:**

ISRCTN Registry ISRCTN33572982; https://tinyurl.com/caa2nw69

**International Registered Report Identifier (IRRID):**

DERR1-10.2196/48014

## Introduction

### Overview

Fungi are ecologically regarded as environmental saprophytes that feed on decaying organic matter. However, over the past 30 years, fungi have transitioned into key etiological agents for difficult-to-manage infections, killing at least 1 million people each year. Yet they remain among the most neglected diseases worldwide [1,2]. The most serious invasive fungal infections often occur in the immunocompromised patients, such as those with HIV, cancer, and organ transplant, all of which have increased dramatically in the last 20 years [2]. Clinical manifestations of fungal infections have ranged from superficial to disseminated diseases with rates of invasive opportunistic fungal infections having upsurged during recent decades. Opportunistic pulmonary fungal coinfections are also emerging due to recent changing trends in predisposing factors and etiology. In Africa, pulmonary fungal coinfections are reported in about 15%-35% of cases, mainly within the cohort of individuals coinfected with HIV and tuberculosis (TB) [3,4]. This is posing enormous challenges to health care professionals, especially in resource-limited settings, where the diagnosis is not precise.

The chronic pulmonary disease has been linked with fungal etiology in the past but is often ignored. However, there is an emerging and interesting twist to fungal etiology, where cross-kingdom interactions appear to impact fungal virulence but are not fully explored. For instance, there are reports that bacteria can influence eukaryotic biology through various roles, such as parasites, commensals, or beneficial symbionts, in addition to acting as sources of new genetic sequences through subtle mechanisms like horizontal gene transfer [4-7]. In this context, the coexistence of fungi with other microbes, such as bacteria, in the same infection niche may unveil highly coordinated metabolic or molecular interaction profiles. This has been shown in chronic wound infections, where fungal-bacterial coexistence disrupts the highly controlled sequence of wound healing [3,8]. In fact, chronic wound microbiome and mycobiome studies reveal that fungal coinfections contribute to impaired wound healing [8]. A study by Mucunguzi and colleagues [9] reported a 22.2% prevalence of pulmonary fungal infections among people living with HIV in Southwestern Uganda. Therefore, it is possible that fungi also affect the outcome of chronic pulmonary diseases but are missed due to the lack of specific clinical or diagnostic signatures, leading to high rates of morbidity and mortality [3,10,11].

In the immunocompromised cohort, pulmonary infections can be exacerbated by a range of pulmonary opportunistic fungal coinfections. Unfortunately, infected individuals often present with symptoms similar to those of the most prevalent diseases, such as pulmonary tuberculosis (PTB) or bacterial pneumonia [3]. This propagates their rapid spread and augments poor prognosis. Hitherto, fungi co-isolated with bacteria have been considered irrelevant and often regarded as environmental contaminants [12]. This is further worsened by limited exposure of clinicians and laboratory fraternity to fungal infection biology. Nevertheless, patients could benefit from the definitive diagnosis of these infections and an exploration of the underlying mechanisms that drive saprophytic fungi to cause diseases in this patient population.

The changing trend of fungal etiology calls for the employment of advanced technology in profiling etiological agents. The synergistic ability of fungi to interact with other microbes, such as bacteria, in health and disease proves complex and can unveil new etiological agents and highlight novel virulence traits and antimicrobial targets. In this project, we propose to study the coexistence of fungal and bacterial microbial communities during chronic pulmonary disease, with a keen interest in underpinning fungal etiological evolution and the predominating interaction relationships that may exist between fungi and bacteria. There is already evidence that such interactions may culminate into properties distinct from those of their individual consortia [4,7,13-17]. Three hypotheses define this study, specifically that the following: (1) the burden of opportunistic pulmonary fungal coinfections is higher than what culture-dependent data suggest; (2) culture-independent data complement culture-dependent data in supporting therapeutic decisions; and (3) fungal-bacterial coexistence influences fungal and bacterial virulence. Thus, through these questions, we hope to reveal elusive interplays between the 2 microbial communities during disease development to explain differences in patient outcomes.

### Significance of the Study

Through this study, we can improve diagnosis and enhance clinical relevance as well as our epidemiological understanding of cross-kingdom etiological interactions. Pilot explorations of polymicrobial interactions, including bacterial-fungal interactions, can mediate a shift in substrate consumption, enzyme production, sexuality, thermostolerance, antimicrobial resistance, metabolism, and virulence [4,7,17-26]. For instance, some Mucorales fungi harbor bacterial endosymbionts that significantly modulate their metabolic profiles and virulence attributes in plants [16,17,27,28]; a similar interaction strategy is suggested in animal hosts [29,30].

During blight light disease of rice seedlings, a saprophytic fungus, *Rhizopus microsporus*, benefits from a toxicogenic alliance formed between this fungus and its endosymbiont bacteria, *Burkholderia rhizoxinica* or *Burkholderia endofungorum*; this alliance enables them to produce a potent anti–beta-tubulin toxin rhizoxin, which is a hepatotoxic cyclopeptide [17,27,31]. In addition, a range of phytotoxins with the potential to mediate virulence, which is thought to be produced by fungi, is a consequence of such interaction [16].

Although the impact of such relationships on clinical outcomes remains unclear, we recently demonstrated that another bacterial endosymbiont, *Ralstonia pickettii*, enabled *Rhizopus microsporus* to modulate innate immune responses in an animal model via a novel secreted factor [29,30]. Removing the endosymbiont using antibiotics rendered *Rhizopus microsporus* completely avirulent. These bioactive compounds are, therefore, important for fungal virulence as well as having potentially exploitable activities as demonstrated by the long history of fungal natural products in medicine, agriculture, and research [32].

### Study Aims

This study aims to determine and characterize the burden, etiological profiles, microbial communities, and interaction relationships established between fungi and bacteria implicated in pulmonary fungal coinfections.

## Methods

### Study Design

This study will be a laboratory-based observational cross-sectional study.

### Study Setting and Population

The study is being conducted at Mbarara Regional Referral and Teaching Hospital (MRRH) in Southwestern Uganda among patients suspected of having PTB.

### Selection Criteria

The target population under study consists of patients suspected of TB at MRRH. Participants will be included if they are 18 years and older, provide consent, and have at least one of the following qualities: presenting with PTB-like symptoms, having no prior history of TB, testing positive or negative on smear test and GeneXpert test, exhibiting lipoarabinomannan antigen positivity along with persistent respiratory symptoms, and being on anti-TB treatment and severely ill yet able to produce sputum. Conversely, HIV-positive or HIV-negative patients who have TB-like symptoms but are on anti-TB treatment with a favorable prognosis will also be included. Patients who are on anti-TB treatment and severely ill but unable to produce sputum, critically ill patients, and pregnant women will be excluded from the study. Patients who are critically ill are excluded because their condition may cause delays in sample collection and obtaining consent, which would impact the recruitment process. Additionally, pregnant women suspected of TB are excluded since they are managed differently according to TB guidelines.

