#### Aim 2: Establishing and Characterizing Microbial Communities Associated With Patients Suspected of Having TB

16S ribosomal RNA (rRNA) gene sequencing will be used to target the bacterial communities present in the same samples, using the same DNA extract, to identify bacterial coinfections. The results obtained will be used to describe the bacterial communities present in the sputum samples and then will be integrated with ITS2 fungal data [13,36-38]. To determine the association with the host phenotypes, the clinical metadata, including but not limited to age, gender, BMI, race or tribe, behaviors, and immune status, will be used to determine the association between fungal and bacterial communities with host phenotypes. For correlations between taxa, a combination of 16S rRNA gene and ITS2 sequencing data from the same samples will be used. Co-abundance patterns of bacteria and fungi will reveal potential interactions between and within fungal-bacterial communities, which can be further explored using DNA-independent methods in Aim 3. Both fungal-fungal, bacterial-bacterial and fungal-bacterial relationships will be interrogated using appropriate software packages, such as SparCC [38,39].

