### Conclusions

We present the protocol of a laboratory-based cross-sectional study involving patients with TB-like symptoms. Through this study, we will explore the metabolic and molecular ecological evolution of invasive opportunistic pulmonary fungal coinfections. This will be achieved by determining the fungal burden, characterizing the associated microbial communities and exploring the potential interaction relationships established between fungal and bacterial etiologies. Through this study, we aim to create diagnostic profile schemes that can be used to infer patient prognostic outcomes in at-risk individuals. Establishing key fungal-bacterial cross-kingdom synergistic relationships is crucial for instituting fungal-bacterial coinfecting etiology.

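### The entry rule makes PTB-like symptoms optional and admits patients already on anti-TB treatment, so the prevalence denominator is not restricted to the suspected-PTB population the protocol names

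*Protocol article*

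**What the plan says.** The Selection Criteria of the protocol article open with the intended population: "The target population under study consists of patients suspected of TB at MRRH". The working rule that follows asks for age 18 or over, consent, and "at least one of the following qualities: presenting with PTB-like symptoms, having no prior history of TB", with further alternatives. One is "testing positive or negative on smear test and GeneXpert test". Another is lipoarabinomannan positivity together with persistent respiratory symptoms. The last is "being on anti-TB treatment and severely ill yet able to produce sputum". A separate sentence adds that "HIV-positive or HIV-negative patients who have TB-like symptoms but are on anti-TB treatment with a favorable prognosis will also be included".

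The exclusions cover severely ill treated patients who cannot produce sputum, the critically ill, and pregnant women.

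Elsewhere the population is narrower. The Objective in the Abstract names presumptive PTB, and Study Setting and Population names patients suspected of PTB. The sample-size section takes its 40% prevalence from patients suspected of TB. The closing Conclusions describe a "laboratory-based cross-sectional study involving patients with TB-like symptoms". For the association analyses, Aim 2 lists "the clinical metadata, including but not limited to age, gender, BMI, race or tribe, behaviors, and immune status".

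**The concern.** A prevalence estimate belongs to the population in its denominator. If one list item is enough and two items carry no symptom or illness term, the rule does not require the symptoms by which the Conclusions define the participants. If patients under treatment for TB are counted together with patients still awaiting a diagnosis, the pooled figure is a weighted mixture. Its weights are set by who happened to attend, because Recruitment Strategy and Retention describes convenience sampling.

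The second risk concerns Aims 2 and 3. Anti-TB drugs are antibacterial and can change the bacterial community that 16S sequencing is meant to describe. Treatment may also go with illness severity and fungal carriage. A fungal-bacterial co-abundance pattern in the pooled sample could therefore partly reflect who was treated. The protocol's own argument makes this relevant: Significance of the Study reports that removing a bacterial endosymbiont with antibiotics made a fungus avirulent.

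**Working it through.** **Step 1. Entry routes side by side** (Selection Criteria)

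| Route | Requires symptoms or illness? | On anti-TB treatment? |
|---|---|---|
| PTB-like symptoms | yes | not stated |
| No prior TB history | no | not stated |
| Smear and GeneXpert, either result | no | not stated |
| Lipoarabinomannan positive | yes (persistent respiratory symptoms) | not stated |
| Severely ill, able to produce sputum | yes (illness) | yes |
| Favourable prognosis | yes (TB-like symptoms) | yes |

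Two routes need no symptom, and two admit treated patients by name. None of the exclusions restores a symptom requirement or removes treated patients who can produce sputum. No section separates treated from untreated patients in the prevalence denominator.

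**Step 2. The plan's own figure.** Inputs from the sample-size section: Z = 1.96, P = 0.4, d = 0.05.

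n = Z² P(1 − P)/d² = 3.8416 × 0.24 / 0.0025 = 368.8, rounded up to 369.

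This reproduces the stated 369. The arithmetic is sound. The difficulty is that the 369 is calculated for suspected TB, while the criteria admit a wider group.

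**Step 3. Possible shift in prevalence.** Let f be the treated share and δ the prevalence in treated patients minus that in untreated patients. Then:

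pooled prevalence = (1 − f) p + f (p + δ) = p + fδ, so shift = fδ.

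The documents give neither f nor δ, so the values below are assumptions. The sign of the shift follows the sign of δ, which is unknown.

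| f | δ = 10 points | δ = 20 points |
|---|---|---|
| 10% | 1 | 2 |
| 25% | 2.5 | 5 |
| 40% | 4 | 8 |

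The article does quote differing fungal prevalences: 22.2% in people living with HIV, and 40% and 70.7% in TB suspects. None compares treated with untreated patients, and their definitions may differ, so they cannot supply δ.

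**Step 4. Precision after separating the groups.** If a share w of the 369 falls outside the untreated symptomatic group (w assumed), the 95% half-width at P = 0.40 is 1.96 × √(0.24 / [369(1 − w)]).

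| w | patients left | half-width (points) |
|---|---|---|
| 0% | 369 | 5.0 |
| 10% | 332 | 5.3 |
| 20% | 295 | 5.6 |
| 30% | 258 | 6.0 |
| 50% | 184 | 7.1 |

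**The case against.** The best defence is that the list works inside the opening sentence, which limits the target to TB suspects, and that recruitment takes place at an HIV/TB clinic under existing diagnostic procedures. On that reading, the either-result item only says that a test result does not bar entry. Most routes also carry a symptom or illness term. This stands in part. A reader might infer that nearly any tested adult qualifies, and the documents do not support that. The opening sentence does not settle the matter, however, because treated patients are admitted by name and the any-one rule leaves symptoms optional.

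Three further inferences also go too far:

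- **Coinfection.** One might say that a fungus in a TB-negative patient is no coinfection. The study's scope is fungal-bacterial, and Previous Findings expressly includes non-TB bacteria, so TB-negative suspects belong in the target.
- **Covariates.** One might say that Aim 2 leaves out treatment and TB result. Its list is expressly open, clinical history is collected, and model terms may be set in a fuller document. The list is no error in itself.
- **Size.** With f = 25% and δ = 20 points the shift equals the planned 5-point margin. Both inputs are chosen, so the match is no evidence.

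It can also fairly be said that treated patients were included on purpose. Removing them from the study population would replace the authors' question with another.

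**Conclusion.** The point holds as a conflict within the document: the stated entry rule is wider than the population to which the prevalence and the conclusions are attributed. It is not a complaint about missing detail. Many participants will be genuine suspects, so the accurate statement is that the denominator is not restricted to presumptive PTB.

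Pooling can bias the prevalence attributed to suspects and confound the bacterial and fungal-bacterial results. The shift is about 1 to 8 points under the assumed shares and differences, against a planned margin of 5. Neither its size nor its direction can be determined from the documents. The confounding rests on anti-TB drugs acting on the bacteria being profiled, and its size is likewise unknown.

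**What to change.** According to the Results section, enrolment was completed in June 2023. The remedy therefore lies in description and analysis; the entry criteria should not be rewritten after the fact.

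1. Reconcile the Selection Criteria with the Objective, Study Setting and Population, the sample-size section and the Conclusions. State which items were mandatory in practice, and describe the enrolled population accurately.
2. Confirm that anti-TB treatment status at sampling was recorded for every participant. The article does not expressly say so.
3. Report prevalence for symptomatic patients not on anti-TB treatment at sampling separately from treated patients, and also by TB test result. Any pooled figure should be labelled as a mixture, with the share of each group shown.
4. Include anti-TB treatment and TB status in the association models. Examine co-abundance within treatment strata where numbers allow.

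The cost is a few sentences of text, some additional tables, and smaller strata with the wider intervals shown above. If treatment status proves incomplete, it would have to be recovered from clinic records or the gap reported as a limitation.

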### Statistical Analysis Plans and Power Calculations (Sample Size)

Based on the preliminary study, the prevalence of fungal coinfections among patients suspected of TB has been previously determined to be 40% using Kish-Leslie formula (n=Z^2^ P (1-P)/ d^2^) for determining the sample size in a cross-sectional study. In this formula, n is the sample size, Z (1.96) is the statistic for the level of confidence, P (0.4) is the estimated prevalence, and d (0.05) is the margin of error for the confidence interval. Using the Open Epi calculator, considering a population of 195,013 for Greater Mbarara, the sample size was determined to be 369 patients. Since we anticipate a 10% dropout rate, we will recruit 406 patients. From these patients, only 2 sputum samples will be collected—an on-spot sample on the day of recruitment and an early morning sample the following day, making a total of 812 samples to be collected. Obtained data will be analyzed using appropriate software, such as GraphPad (GraphPad Software Inc), Stata (StataCorp), or Epi Info (Centers of Disease Control and Prevention), among many others.

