### Recruitment Strategy and Retention

Patients will be recruited by convenient sampling as they report for medical services at the HIV/TB clinic of MRRH. The recruitment of the participants will follow the existing diagnosis and point-of-care procedures at both study sites. The clinic receives an average of 10 new cases per day. Considering both our inclusion and exclusion criteria, we hope to recruit an average of 4 patients per day, resulting in an average total of 88 patients per month. This recruitment plan is achievable based on the rate of patients’ inflow at the clinic. Additionally, sputum sample collection is not an invasive method that would scare away patients, so we do not anticipate any major challenges with patient retention. However, we will factor in a possible 10% dropout rate among patients, and thus, the final sample size will be increased by 37 more patients, resulting in a total of 406 patients, as previously mentioned.

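### Minor arithmetic error: 406 allows for a 9.1% loss, not the stated 10% (369 × 1.10 was used instead of 369/0.90 = 410); the effect on precision is negligible

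*Protocol article*

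**What the plan says.** The section on statistical analysis plans and power calculations sizes the study on the precision of a single prevalence. It uses the Kish-Leslie formula with these inputs: "Z (1.96) is the statistic for the level of confidence"; "P (0.4) is the estimated prevalence"; "d (0.05) is the margin of error for the confidence interval". It also enters a finite population, "considering a population of 195,013 for Greater Mbarara", and reports that "the sample size was determined to be 369 patients". It then adds the dropout allowance: "Since we anticipate a 10% dropout rate, we will recruit 406 patients".

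The section on recruitment strategy and retention shows how the allowance was made: "the final sample size will be increased by 37 more patients, resulting in a total of 406 patients". The two sections agree with each other. The figure of 406 also appears in the abstract and among the expected deliverables, and twice 406 gives the stated 812 samples.

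Two further statements bear on the point. The sputum samples are "an on-spot sample on the day of recruitment and an early morning sample the following day", and the Results section reports that enrolment was completed in June 2023.

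**The concern.** Dropout happens among the patients who are recruited. To finish with 369 after losing a fraction of 0.10, one divides 369 by 0.90. Adding 10% of 369 takes the percentage of the wrong base and always gives too few. Here the stated recruitment number does not meet the stated requirement under the protocol's own dropout assumption.

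What is at stake is the match between three published figures: 369 required, 10% lost, 406 recruited. They cannot all hold together if a dropout gives no data. A results paper that repeats them would carry the mismatch forward.

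**Working it through.** **Inputs**, all from the sample-size and recruitment sections: Z = 1.96, P = 0.4, d = 0.05, N = 195,013, requirement 369, dropout 10%, addition 37, total 406.

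**1. Reproduce the requirement.**
- Kish-Leslie: Z²P(1−P)/d² = 1.96² × 0.4 × 0.6 / 0.05² = 368.8, rounded up to 369.
- With the finite population correction: N·P(1−P) / [(d²/Z²)(N−1) + P(1−P)] = 368.1, rounded up to 369.

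Both give the stated 369.

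**2. Reproduce the total.**
- 0.10 × 369 = 36.9, so 37 extra; 369 × 1.10 = 405.9, rounded up to 406.

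This matches both the 37 and the 406, so the method used is clear.

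**3. Apply 10% loss to those recruited.**
- 406 × 0.90 = 365.4, so about 365 remain, which is 4 below 369.
- Loss that 406 can absorb while leaving 369: 37/406 = 9.1%.
- Number needed for 369 after 10% loss: 369/0.90 = 410, that is 41 extra; check: 410 × 0.90 = 369.

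**4. Effect on precision.** Half-width = 1.96 × √(P(1−P)/n) at P = 0.4.

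| Evaluable n | Half-width (points) |
|---|---|
| 369 | 5.00 |
| 365 | 5.03 |

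The change is about 0.03 of a percentage point. The gap in recruits is 4/406 = 1.0%.

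**5. Sensitivity to what a dropout means.** If 10% drop out, about 41 of the 406 are affected. If at least 4 of these 41 have a usable first sample that counts towards the prevalence, 365 + 4 = 369 and there is no shortfall.

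**The case against.** The strongest case on the other side has four parts.

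- **A dropout need not be non-evaluable.** The first sputum sample is taken on the day of recruitment and the design is cross-sectional. A patient who does not return the next day has already given material for culture and sequencing. Only 4 of about 41 such patients need count. This stands: the article does not say how patients with one sample are handled, so the shortfall is conditional. It does not justify the calculation, because an allowance for dropout has a purpose only if some dropouts are lost to the analysis.

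- **The 10% is a loose contingency.** The recruitment section presents it as a possibility and expects no major retention problem. The difference between 9.1% and 10% is likely smaller than the uncertainty in the assumption. This stands as an argument about size, not about correctness.

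- **The assumed prevalence matters more than four patients.** With 365 patients, other prevalences quoted in the article, for differing populations or definitions, give half-widths below 5 points: about 4.9 at 35%, 4.3 at 22.2%, 4.7 at 70.7% and 2.8 at 92%. This also stands.

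- **The figure of 406 is used consistently.** That is true, but consistent repetition does not show that the step behind it is right.

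A reader might go further and infer that the study fails to deliver its 5-point margin, or that 410 should now be recruited. The documents support neither. The margin is stated as 0.05, and 0.0503 is the same value at that precision. Enrolment is reported as complete, so a higher target is no longer open.

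**Conclusion.** The point holds as a minor arithmetic error. The 10% allowance was taken as a percentage of the evaluable number instead of the recruited number, giving 406 where 410 follows from the protocol's own assumptions. The size is 4 patients, about 1% of the sample, and a half-width of 5.03 rather than 5.00 points.

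The shortfall rests on three assumptions: exactly 10% of those recruited are lost, each of them gives no usable sample, and the prevalence is 0.4. If the loss is 9.1% or less, or if a few of the dropouts have a usable first sample, 369 is reached. The slip does not undermine the sample size or any planned conclusion.

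**What to change.** Keep 406 as the number recruited and 812 as the number of samples planned. In the sample-size section, replace the dropout sentence with a statement on these lines: *406 patients recruited allows for about 9% non-evaluable patients; with 10% loss about 365 are evaluable, giving about ±5.03 points at a prevalence of 0.4.* In the recruitment section, describe the 37 additional patients in the same way, as covering a loss of about 9%.

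The cost is a sentence in each of two sections and a very slightly less favourable stated precision. No change to design, recruitment or analysis is needed.
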